#### **7.4 Prior and concomitant medication / treatments**

All medication taken/treatments obtained before study start (initiated before study start) is termed prior medication/treatments.

Specific prior medication/treatments, including oral phosphate binders, ESA, iron preparation, aluminum containing medication, Vitamin D & calcium supplements, anti-osteoporotic medications, or other drugs that affect serum phosphorus level, during the past 3 months prior to study enrollment which meet the criteria below are considered relevant to the study indication and should be collected.

Any concomitant medication taken in addition to the study treatments and is considered relevant to influence serum phosphorous and/or iron levels should be collected throughout the study.

Other concomitant medications taken in addition to the study treatments which not fall into the table of specific medications, only minimal information will be collected throughout the study.

#### **7.5 Prohibitions and Precautions**

Subjects are prohibited to participate in clinical trial of other interventional drug or device throughout the study period.

Following precautions should be taken during the study:

- Subjects should be instructed to avoid taking ferric citrate concurrently with Aluminum-containing drugs.
- When using oral medications where a reduction in the bioavailability of the drug may cause clinically significant effect on its safety or efficacy, consider to administer the drug 2 hours before or after taking ferric citrate.
- The safety information of ferric citrate for pregnant and breastfeeding women has not been established. Female subjects of child-bearing potential are encouraged to take appropriate contraceptive procedures to avoid pregnancy during the study period.
- Caution should be taken to assess patients' overall condition if prescribing ferric citrate to patients with ferritin >800 ng/mL or TSAT >50%. Discontinue using of iron therapy if the symptom of iron overload is observed.

#### **7.6 Blinding**

This is an open-label, single arm study. No blind setting will be applied in this study.

### **8 STUDY PROCEDURES BY VISIT**

#### **8.1 Visit 1: Enrollment and Baseline Visit**

Procedures are to be performed at Visit 1 including obtain signed Informed Consent Form from the subject, confirm eligibility, assign subject identifier, obtain demographic data, record CKD and other medical history, record Prior/Concomitant medications, perform physical examinations and obtain vital signs, perform baseline clinical laboratory tests, and study drug dispensing

#### **8.2 Visit 2 to Visit 12 and Visit 14**

The monthly visits will follow individual Investigator's routine clinical practice for each subject. However, it is suggested the monthly visits to be scheduled at regular intervals throughout the study period, e.g. approximately every 30 days.

Procedures are to be performed from Visit 2 through Visit 12, and the follow-up visit 14 including record concomitant medications, perform physical examinations and obtain vital signs, check for

adverse events, perform clinical laboratory test results, accountability on returned drugs and compliance check, and study drug dispensing

### **8.3 Visit 13: End-of-Treatment /Early Termination Visit**

Procedures are to be performed at EOT including record concomitant medications, perform physical examinations and obtain vital signs, check for adverse events, perform clinical laboratory tests, and return all study drugs and empty containers

## **9 STATISTICS**

A description of statistical methods is presented below and will be described in more detail in the Statistical Analysis Plan (SAP).

### **9.1 Determination of Sample Size**

Since this is a single-arm observational study, and the major purpose is to collect long-term safety and efficacy of ferric citrate, the sample size of 200 subjects is driven by a post-approval commitment to the regulatory authority. Safety profile for a minimum drug exposure in 100 evaluable patients for 6 months and 1 year are required by the Taiwan regulatory authority. Taking reference from previous long-term extension study, total of 168 subjects were dosed in the 307 study and 125 subjects (74%) completed the 48 weeks treatment. Enrollment of 200 subjects in the present study should be sufficient to collect the long-term safety profile for 1 year in at least 100 patients.

### **9.2 Definition of Analysis Sets**

Subjects will be categorized into the following populations to meet various study purposes.

Safety population: all subjects who are exposed to at least one dose of the study medication.

Full analysis set (FAS): the FAS population is defined as the subjects who satisfy all eligibility criteria, have taken at least one dose of study medication, and have at least one post treatment evaluation for efficacy.

Safety assessment will be determined on safety population. Baseline and demographic characteristics analyses will be performed on the safety population. Efficacy assessment will be performed on both safety and FAS populations, where efficacy conclusion will be made on FAS. For exploratory endpoints, descriptive statistics will be performed on both safety and FAS populations.

### **9.3 General Statistical Considerations**

This is an observational study, all analysis will be performed based on descriptive statistics. No hypothesis testing will be performed.

Descriptive statistics such as mean, standard deviation, median, minimum and maximum values will be presented for the continuous variables and the number of patients and percentage will be presented for the categorical variables.

All therapies documented will be coded using the World Health Organization – Drug Dictionary (WHO-DD). Medical history, any diseases and AEs will be coded using the latest MedDRA version. The SAS® package (SAS® Institute Inc., USA, and Version 9.2 or later) will be used for statistical evaluation.

### **9.4 Analysis of endpoint**

Safety assessment: This to assess the safety profiles from baseline to the EOT. Safety profiles will only be assessed by monitoring and recording the incidence of treatment-emergent adverse events

(TEAEs) and serious TEAEs, whether related to study treatment or not, as determined by changes in clinical laboratory tests (i.e., hematological tests and biochemical tests, including iron panels), physical examinations, vital signs, standard 12-lead electrocardiogram and any other untoward medical events during the study period. All subjects who receive at least one dose of study medication will be evaluated for safety.

TEAEs are defined as adverse events with an onset date on or after the first dose of study treatment. AEs with missing onset dates will be assumed to be treatment-emergent. Incidence of TEAEs will be summarized by the number, percentage, severity, and suspected relationship to study drug according to system organ class and preferred term using the MedDRA coding system.

**Efficacy assessment:** This is to describe the effectiveness of ferric citrate for the control of serum phosphorus concentration and achievement rate of target phosphorus level throughout 12 months of treatment. Treated patients who had an efficacy assessment at least once will be included in the full analysis set.

- Time-course changes of serum phosphorus levels from baseline to the end-of-treatment will be summarized according to each available observation visits. Continuous variables will be presented as mean  $\pm$  standard deviation or median with interquartile range, as appropriate.
- Proportion of subjects achieved the target range of serum phosphorus ( $\geq 3.5$  mg/dL and  $\leq 5.5$  mg/dL) from baseline to the end-of-treatment will be tabulated or plotted, as appropriate.

**Exploratory endpoint:** The following parameters will be explored:

- Time-course change of serum calcium and intact plasma parathyroid hormone (iPTH): Serum calcium and iPTH will be summarized descriptively as observed values at baseline, at every observation point, and at EOT. Changes from baseline will be descriptively summarized at completion of Visit 4 (Month 3), Visit 7 (Month 6), at Visit 13 (Month 12), and at EOT (including early termination).
- Time-course changes of iron-parameters from baseline to EOT: Serum iron, ferritin, TSAT, and TIBC will be summarized descriptively as observed values at baseline, every observation point, and EOT. Changes from baseline will be descriptively summarized at completion of Visit 4 (Month 3), Visit 7 (Month 6), at Visit 13 (Month 12), and at EOT (including early termination).
- Time-course changes of hemoglobin from baseline to EOT: Hemoglobin will be summarized descriptively as observed values at baseline, every observation point, and EOT. Changes from baseline will be descriptively summarized at completion of Visit 4 (Month 3), Visit 7 (Month 6), at Visit 13 (Month 12), and at EOT (including early termination).
- Changes in dose of IV iron and ESA from baseline to EOT: Dose of ESAs and intravenous iron preparations will be summarized descriptively at baseline, every observation point, and EOT.
- Treatment adherence: Dose of study drug dispensed and actually taken between each visit will be recorded. Proportion of the prescribed dose versus the dose actually taken at each time point will be calculated and summarized as percentages. Accumulated dose of individual subjects will be summarized by the end of treatment or at early termination.

Details will be specified in the statistical analysis plan (SAP).

## **9.7 Handling of Missing Data**

Missing observations will not be imputed in the analysis. All statistics will be performed on available actual data.

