| Statistical Analysis | 
Safety assessment:
 Treatment-emergent adverse events (TEAEs) will be summarized by system organ class, preferred term, severity, and suspected relationship to study drug. Clinical laboratory tests and vital signs of observed values and changes from baseline will be summarized using descriptive statistics. Physical examination findings and ECGs will also be summarized descriptively.
 
Efficacy assessment
 
 
• The mean and the 95% confidence interval for the mean values are to be calculated at for each observation day and at the EOT.
 
• Proportion of subjects achieved the target range of serum phosphorus (<math>\geq 3.5</math> mg/dL and <math>\leq 5.5</math> mg/dL) from baseline to the end-of-treatment will be tabulated or plotted, as appropriate.
 
 
Exploratory analyses
 
 
• Time-course change of serum calcium and iPTH: Changes in serum calcium and iPTH will be summarized descriptively as observed values and as changes from baseline
 
• Time-course changes of iron-parameters: Changes of iron parameters will be summarized descriptively as observed values and as changes from baseline
 
• Time-course changes of hemoglobin: Changes in hemoglobin will be summarized descriptively as observed values and as changes from baseline
 
• Change in dose of IV iron and ESA: Changes in dose of IV iron and ESA from baseline to EOT will be summarized descriptively.
 
• Treatment adherence: Descriptive statistics of the prescribed dose and the dose actually taken at each time point will be calculated.
 
 |

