### **4 STUDY VARIABLES**

#### **4.1 Variables to Determine the Safety**

The safety assessment is to assess the safety profiles from baseline to the end-of-treatment (EOT). Safety profiles will be assessed by monitoring and recording the incidence of treatment-emergent adverse events (TEAEs) and serious TEAEs, whether related to study treatment or not, as determined by changes in clinical laboratory tests (i.e., hematological tests and biochemical tests, including iron panels), physical examinations, vital signs, standard 12-lead electrocardiogram and any other untoward medical events during the study period. All subjects who receive at least one dose of study medication will be evaluated for safety.

To ensure complete safety data collection, all AEs occurring after signing the Informed Consent form, including any pre-treatment and post-treatment periods required by the protocol, shall be recorded. TEAEs will be defined as adverse events (AEs) with an onset date on or after the first dose of study treatment. AEs with missing onset dates will be assumed to be treatment-emergent. The incidence of TEAEs (any TEAE, serious TEAEs, drug-related TEAEs, serious drug-related TEAEs, and TEAEs leading to treatment discontinuation, or death) will be summarized, respectively. If a TEAE is reported more than once by a subject during the study, the one with the greatest severity will be included in the summary tables. A TEAE will be considered drug-related if the Investigator indicates that the event is “possibly”, “probably”, or “definitely” related or if the relationship is missing.

The variables used to describe TEAEs are listed below:

- 1) Clinical laboratory tests will be recorded at every visit including essential examinations and optional examinations. Essential examinations consist of routine hospital examinations and study-mandatory examinations. The essential examinations will be performed and collected according to protocol schedule at every visit unless otherwise stated (i.e., serum aluminum performed at Visit 1 and EOT [Visit 13 or early termination]; iPTH performed at Visit 1, Visit 4, Visit 7, Visit 10, and EOT [Visit 13 or early termination]). Optional examinations, although not mandated, will be collected and assessed if results are available following routine practice.

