### **6.3 Withdrawal Criteria**

Subjects are free to withdraw from the study at any time, without prejudice to their continued care. A subject may be removed from the study at any time if any of the following events occurs:

- Subject request
- Treatment failure
- Investigator's discretion for the best interest of subject
- Intercurrent illness or medical event necessitating study drug discontinuation

If the subject withdraws, the final evaluations will be performed as completely as possible. A clear and concise reason for withdrawal should be recorded in the case report form (CRF). If the subject is withdrawn because of an AE, the subject should be followed until the AE resolves.

If a subject has serum phosphorous level  $>8.0$  mg/dL in two consecutive monthly visits, not due to subject-reported non-compliance, the subject will be considered a treatment failure and will discontinue from the study.

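### By-visit phosphorus means and target rates drift in the drug's favour because patients discontinued for high phosphorus drop out of later visits; the end-of-treatment summary is largely protected

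*Protocol*

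**What the plan says.** Section 6.3 (repeated in the synopsis) sets the trigger as phosphorus above 8.0 mg/dL "in two consecutive monthly visits, not due to subject-reported non-compliance". The consequence is that "the subject will be considered a treatment failure and will discontinue from the study". At withdrawal, section 6.3 asks for final evaluations only; no later scheduled phosphorus values are described.

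Section 9.4 gives two phosphorus summaries. The levels "will be summarized according to each available observation visits". The proportion within 3.5 to 5.5 mg/dL "from baseline to the end-of-treatment will be tabulated or plotted, as appropriate". The synopsis adds that the mean and its 95% confidence interval "are to be calculated at for each observation day and at the EOT". Section 9.4 describes the aim as control and target achievement over the full 12 months of treatment.

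Section 9.7 fixes the missing-data rule for all of these: "Missing observations will not be imputed in the analysis. All statistics will be performed on available actual data".

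Section 9.2 bases the efficacy conclusion on the full analysis set (FAS). Sections 4.1 and 9.4 treat EOT as Visit 13 or the early-termination visit. No section says how a treatment failure counts at visits after removal.

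**The concern.** The removal rule is triggered by the efficacy variable itself, so missingness at later visits depends on the outcome by design. A failed patient remains in the FAS in name but contributes nothing to any later visit. The by-visit mean falls and the by-visit target rate rises as failures accumulate, even if no patient's phosphorus changes.

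This is a single-arm study, so no control arm would show the same drift. A reader of the month-by-month curve cannot separate selection from durable control, and durability over 12 months is what the efficacy summary sets out to describe.

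**Working it through.** **The protocol's own retention figure.** Section 9.1 cites 125 of 168 completing 48 weeks: 125/168 = 74.4%, and 200 × 0.744 = 149, above the required 100. The figure reproduces. It gives total retention only and does not say how many of the 168 − 125 = 43 non-completers left for high phosphorus, so it cannot size this bias.

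**Simple accounting.** Let p be the true target rate and f the fraction removed, and suppose none of those removed would be in target. The available-data rate is then p/(1 − f).
- p = 50%, 20 of 200 removed: 100/180 = 55.6%, or +5.6 points.
- p = 50%, 10 of 200 removed: 100/190 = 52.6%, or +2.6 points.

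**Simulation with no true change.** There were 400,000 patients per scenario and 12 monthly values, each a constant patient mean plus within-patient noise. Patients were removed after two consecutive values above 8.0 mg/dL.

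Inputs:
- From the protocol: the 8.0 mg/dL rule, the 3.5 to 5.5 mg/dL target and the available-data rule. Section 2 gives anchors for the long-run mean: 4.69 and 5.38 mg/dL are the end-of-study means at 6 and 4 g/day in the Taiwan pivotal study, and 6.95 mg/dL is a baseline mean there.
- Assumed: a mean of 6.0 as an intermediate case, total SD 1.5 mg/dL, within-patient correlation 0.5, every trigger enforced, no other dropout.

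| Long-run mean (mg/dL) | Removed as failures | Target rate, month 1 | Month 12, available data | Drift (points) | Month 12, failures kept as not in target | Drift in by-visit mean (mg/dL) | EOT mean / target rate |
|---|---|---|---|---|---|---|---|
| 4.69 | 1.3% | 49.1% | 49.5% | +0.4 | 48.9% | −0.03 | 4.71 / 48.9% |
| 5.38 | 5.0% | 42.7% | 44.5% | +1.8 | 42.4% | −0.10 | 5.45 / 42.4% |
| 6.0 | 13.0% | 32.1% | 36.2% | +4.0 | 31.7% | −0.22 | 6.14 / 31.7% |
| 6.95 | 37.4% | 15.6% | 23.1% | +7.5 | 14.8% | −0.56 | 7.29 / 14.8% |

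Drifts are taken from unrounded values. The simple formula gives nearly the same result: at mean 6.0, 32.1%/(1 − 0.130) = 36.9% against 36.2% simulated. The formula is slightly high because a removed patient would sometimes have been in target.

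**Sensitivity to the assumptions.**
- Adding 20% other, non-informative dropout gives drifts of +0.5, +1.9, +3.9 and +7.4 points at the four means.
- Varying the SD over 1.2 to 1.8, and the correlation over 0.4 to 0.6 in part of the grid, gives +0.2 to +1.2 points at mean 4.69, +0.6 to +2.9 at 5.38, +1.6 to +6.2 at 6.0, and +3.9 to +10.6 at 6.95 to 7.0. The share removed runs from 0.2% to 46%.

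**EOT row.** It retains failures' last values. At mean 6.0 its target rate is 31.7% against a true 32.1%, and its mean is 6.14 against a true 6.00, which goes against the drug. The month-12 by-visit mean in the same scenario is 6.00 − 0.22 = 5.78, so the two summaries differ by 6.14 − 5.78 = 0.36 mg/dL with no stated explanation.

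**Which remedy restores the true rate.** Counting only treatment failures as not in target stays within 1 point of the true rate in the table, and at most about 3 points below it across the wider grid. Counting every discontinuation as not in target, with 20% other dropout, turns a true 42.7% into 34.0% (−8.7 points) at mean 5.38, and 49.2% into 39.2% (−10.0 points) at mean 4.69.

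**The case against.** The strongest reply has four parts.

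- **Low stakes.** Phosphorus is secondary, the primary endpoint is safety, section 9.3 rules out hypothesis tests, and enrolment is set by a safety-exposure commitment. This stands and lowers the priority. It does not remove the point, because section 9.2 still plans an efficacy conclusion and the by-visit curve is part of its evidence.
- **EOT already covers it.** This stands for the EOT row. A reader might infer that every phosphorus result is biased in the drug's favour. The documents do not support that, since EOT includes early termination and its mean errs slightly the other way. The by-visit series is not protected.
- **The denominator is open.** Section 9.4 names no denominator for the target rate, and details are deferred to the SAP. This stands in part. However, section 9.7 applies to all statistics, so an SAP that follows it reproduces the drift and one that corrects it departs from the protocol.
- **The size is uncertain.** This stands. At the on-treatment means that section 2 reports, the drift is small. The simulation holds each patient's mean constant although section 7.2 allows titration, and it enforces every trigger although patients with self-reported non-compliance are exempt. Both could reduce the drift in practice. Other dropout could add to it or offset it.

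A reader might also rescale a completer target rate to all 200 enrolled and call the difference the bias. That scores every dropout as a failure, whatever the reason, and does not isolate removal for high phosphorus.

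**Conclusion.** The point holds for the by-visit means and target proportions, and should be fixed. Its direction follows from sections 6.3 and 9.7 alone.

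Its size does not follow from the documents. With SD 1.5 mg/dL, correlation 0.5 and no true change, the month-12 target rate is overstated by about 0.5 to 2 points if the long-run mean is 4.7 to 5.4 mg/dL, and by about 4 to 7 points if it is 6 to 7 mg/dL. A reader might infer that the curves are bound to show a marked improvement. That would need a failure rate the protocol does not give, and under good control the effect is negligible. The safety endpoint is not affected by this point.

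**What to change.** In sections 9.4 and 9.7, and in the SAP:

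1. Report the by-visit target proportion with protocol-defined treatment failures kept in the denominator as not in target at all visits after removal, with a 95% CI.
2. Estimate mean phosphorus by visit with a likelihood-based repeated-measures model on all observed values, including the early-termination value. This suits removal that depends on phosphorus values already observed.
3. Keep the observed-case tables as supportive, showing n and the cumulative number of treatment failures at each visit.
4. If discontinuation for any reason is counted as not in target, make it at most a labelled sensitivity analysis, because it can make stable control look like deterioration.

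The withdrawal rule stays as it is and no new data are needed. The cost is revised wording, a little more analysis work and a slightly less favourable reported rate.

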## **10 ASSESSMENT OF SAFETY**

### **10.1 Adverse Events**

An adverse event (AE) is any untoward medical occurrence in a patient or clinical investigation in which a subject is administered with a pharmaceutical product which does not necessarily have a causal relationship with this treatment. An AE can therefore be any unfavorable and unintended sign (including an abnormal laboratory finding), symptom, or disease temporally associated with the use of a medicinal (investigational) product, whether or not related to the medicinal (investigational) product. Any worsening (i.e., any clinical significant adverse change in frequency and /or intensity) of a preexisting condition, which is temporally associated with the use of the investigational product, is also an AE.

To ensure complete safety data collection, all AEs occurring after signing the Informed Consent form, including any pre-treatment and post-treatment periods required by the protocol, must be recorded in the CRF even if no investigational product was taken but specific study procedures were conducted. Signs or symptoms of the condition/disease for which the investigational product is being studied should be recorded as AEs only if their nature changes significantly or their frequency or intensity increases in a clinically significant manner as compared to the clinical profile known to the Investigator from the subject's history or the Baseline Period.

Adverse events will be collected by means of a standard question, i.e., "Have you had any health problems since the previous visit?" This question will be asked to the subject at every time point after the initial dose of study drug is dispensed. When recording an AE, Investigator is strongly encouraged to use the overall diagnosis or syndrome using standard medical terminology, rather than recording individual symptoms or signs. The CRF and source documents should be consistent. Any discrepancies between the subject's own words on his/her own records (e.g., diary card) and the corresponding medical terminology should be clarified in the source documentation.

An AE should be followed until it has resolved, has a stable sequelae, the Investigator determines that it is no longer clinically significant, or the subject is lost to follow-up. If an AE is still ongoing at the end of the study for a subject, follow-up should be provided until resolution/stable level of sequelae, the Investigator no longer deems that it is clinically significant, or until the subject is lost to follow-up. If no follow-up is provided, the Investigator must provide a justification. The follow-up should be continued for approximately 1 month after the subject has discontinued their IP.

